### Outcome assessment

The primary outcome measure will be the completion of ACP documentation. We will specifically examine the completion of various sections of the ACP (Appointment of MTDM and Support Person, Values and Instructional Directives). The following secondary outcomes that will be assessed will be attitudes towards ACP, congruence in communication and preparedness for decision-making*.*

#### Data collected and measures used

Table 3 outlines the measures used at baseline and post-intervention. The baseline questionnaire will include the patient’s and caregiver’s demographic information, including age, sex, marital status, place of birth, the relationship between patient and caregiver, primary cancer diagnosis, and length of time living with the diagnosis. Patients will be asked if they had previously discussed prognosis with their doctor.

**Table 3 Tab3:** Measures used pre and post UC and VDST

Measures used	Patient		Caregiver	
	Baseline: Pre UC/VDST	Post UC/VDST	Baseline: Pre UC/VDST	Post-UC/VDST
Demographics	**×**		**×**	
DASS-21	**×**			
ACP Attitudes	**×**	**×**	**×**	**×**
CCAT	**×**	**×**	**×**	**×**
PDMS	**×**	**×**	**×**	**×**

*DASS-21* Depression, Anxiety and Stress Scale, *CCAT* Cancer Communication and Assessment Tool, *PDMS* Preparation for Decision Making Scale

The following variables and outcomes will be assessed:
*Baseline Depression, Anxiety and Stress scores*. The DASS 21 scale is a validated 21 item self-reported questionnaire designed to measure the negative emotional states of depression, anxiety, and stress [35]. Evaluation of the DASS 21 in cancer has shown acceptable internal consistency reliability for the Depression subscale (α = .90) and Anxiety subscale (α = .70) with construct validity to measures of suicidal ideation, quality of life, self-rated health, and depressed mood [36].*Attitudes towards ACP*. Understanding of, opportunities, distress, and confidence related to ACP will be assessed using a previously designed and tested questionnaire comprising nine patient and eight caregiver items, measured on a 10 point Likert scale [32].*Congruence in decision-making* will be measured using the Cancer Communication Assessment Tool for Patients and Families (CCAT-PF). CCAT-PF consists of 18 items and measures congruence in patient-caregiver communication with the analogous patient (CCAT-P) and family (CCAT-F) instruments, exploring preferences, values, and experiences in treatment decision-making. The CCAT-PF demonstrated internal reliability coefficients for the CCAT-P (α = .52), CCAT-F (α = .50), and CCAT-PF (α = .60). Higher CCAT-PF scores are significantly correlated with greater patient depression and perceived family conflict, lower patient-caregiver assessment and well-being, and less expressiveness and family cohesion [37].*Preparation for decision-making* will be measured using the Preparation for decision-making scale, a validated scale assessing patient and caregiver perception of an intervention’s usefulness. Psychometric analysis has shown Alpha coefficients for internal consistency ranging from 0.92 to 0.96 and that the scale discriminated significantly between patients who did and did not find a decision aid helpful (*p* < 0.0001) [38].

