**Fig. 1 Fig1:**
[figure not shown]
Study procedure

Patients and caregivers will be consented individually by the research facilitator and will complete individual baseline pre-questionnaires (Supplementary file). Participants will then be randomised as dyads to either the UC or VDST arm. All participants will be advised that participation is voluntary, they may withdraw at any time, and that all information gathered will be treated in the strictest confidence. Patients and caregivers will also be advised that non-participation will not affect their care or their choice to complete an ACP.

Patients from both groups will be advised to discuss their completed ACP with their general practitioner or treating specialist to clarify any questions. The completed ACP will have to be signed, witnessed and returned with the post-questionnaire in a stamped return envelope. Participants will be advised to return the questionnaires even if they choose not to complete the ACP. Participants will receive two telephone call prompts at two-week intervals on completion of the intervention as a reminder to return the completed documents. Returned ACP’s will be scanned into the hospital’s electronic record system, and a copy returned to the patient.

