### Quality standards

#### Randomization and blinding

Randomization occurs after completion of baseline assessments. An independent randomization administrator will complete randomization at the individual level using a computer-generated random number sequence in blocks of 6 in 1:1 ratio and with concealed allocation using numbered envelopes. The nature of the intervention makes it impossible to blind study participants. Treatment group assignments will therefore be non-blinded, but outcome assessors will be blinded to allocation.

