## Statistical analysis

Descriptive statistics will be presented as frequencies and relative frequencies for categorical variables, mean and standard deviation for normally distributed continuous variables, or median and interquartile range for continuous variables that are not normally distributed. We will examine secondary outcomes between the two groups comparing pre and pre and post-test intervention changes with Chi-square or Fisher’s exact test for categorical variables and two-sample *t*-tests or Mann-Whitney test for continuous variables.

Additionally, multiple linear regression will be performed, addressing the effect of socio-demographic and clinical variables to explore factors associated with the rates of completion of ACP All results obtained will be presented at a confidence interval of 95%. Thus *p* < 0.05 is assumed to be statistically significant. The statistical software SPSS 23 will be used in this analysis.

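### The Preparation for Decision Making Scale rates an intervention's usefulness but is scheduled before any intervention, so its baseline and change scores are not interpretable as described

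*Protocol article*

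**What the plan says.** Four places in the protocol article bear on this.

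- **Construct.** Under Data collected and measures used, the PDMS is "a validated scale assessing patient and caregiver perception of an intervention’s usefulness". The validation evidence given there is that "the scale discriminated significantly between patients who did and did not find a decision aid helpful".
- **Schedule.** Table 3, titled "Measures used pre and post UC and VDST", marks the PDMS in all four columns: baseline and post, for patient and for caregiver. The baseline columns are labelled "Baseline: Pre UC/VDST".
- **Order of events.** The Randomization and blinding section states: "Randomization occurs after completion of baseline assessments". The Study procedures section agrees. After consent and the individual baseline questionnaires, it says: "Participants will then be randomised as dyads to either the UC or VDST arm".
- **Analysis.** The Statistical analysis section says the secondary outcomes will be examined between the two groups by "comparing pre and pre and post-test intervention changes". It does not name individual scales. Preparedness for decision-making is one of the three secondary outcomes listed under Outcome assessment.

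**The concern.** A scale that asks how useful an intervention was needs an intervention to refer to. At baseline neither usual care nor the video tool has been delivered, so the respondent has no defined object to rate. Some may skip items, some may guess, and some may rate unrelated information they received earlier. A change score subtracts those answers from the post-intervention rating, which does have an object.

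Three things are at stake. The baseline mean and the within-arm change would be reported without a clear meaning. The between-arm comparison may be less precise than one based on post scores alone. And patients with incurable cancer and their caregivers would complete a form that adds little.

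**Working it through.** **1. Passages side by side.** The construct and its validation both presuppose exposure to an intervention. Table 3 places the scale before exposure, and two sections confirm that baseline precedes allocation. The baseline marks do not look like a default of the table layout, because the DASS-21 is marked at patient baseline only. The table therefore does separate measures taken once from measures taken twice. The analysis sentence covers the secondary outcomes as a group and makes no exception for the PDMS.

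**2. Is the between-arm comparison biased?** Write B for the baseline score and P for the post score. The expected between-arm difference in change is

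E(P − B | VDST) − E(P − B | UC) = [E(P | VDST) − E(P | UC)] − [E(B | VDST) − E(B | UC)].

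B is recorded before randomisation, so the second bracket is zero in expectation. The mean difference in change estimates the same quantity as the mean difference in post scores. Baseline items left blank would reduce the number of usable change scores, but they too are fixed before allocation and cannot favour an arm. There is no bias from this source.

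**3. What does it do to precision?** The article gives no power figure for the PDMS, so there is none to reproduce. The assumptions, none of which is in the documents, are equal pre and post standard deviations and a pre-post correlation r.

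- Variance of change = 2(1 − r) × variance of the post score.
- Take a difference with 80% power on post scores (two-sided 5%). Its standardised distance is 1.96 + 0.84 = 2.80.
- Power on change scores = Φ(2.80 / √[2(1 − r)] − 1.96).

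| r | 2(1 − r) | 2.80 / √[2(1 − r)] | Power on change |
|---|---|---|---|
| 0 | 2.0 | 1.98 | about 51% |
| 0.2 | 1.6 | 2.21 | about 60% |
| 0.5 | 1.0 | 2.80 | 80% |
| 0.8 | 0.4 | 4.43 | about 99% |

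The sample size cancels out of this formula, so the result does not depend on how many dyads are retained.

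**4. Cross-check at the planned size.** With the protocol's 43 per group and an assumed standardised post difference of 0.6, power on post scores is 79%. Power on change scores is 50%, 59%, 79% and 99% at the same four correlations. The pattern is the same: a loss below r = 0.5, none at 0.5, and a gain above it.

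**The case against.** The strongest counter-arguments are these.

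- **The baseline form has not been seen.** It is in a supplementary file that is not at hand, and the abstract calls the questionnaire one developed for the study. The baseline items could have been reworded to ask how prepared the respondent feels now. This stands as a limit. A reader might infer that the baseline and change scores have no meaning at all, but the documents do not support that. They support only that the use of the scale at baseline is unexplained and does not fit the construct as described. The article mentions no rewording, and the validation it cites is for a scale that rates an intervention.
- **The analysis sentence is general and garbled.** It never names the PDMS, so applying it there is an inference. The inference is a natural one, since Table 3 supplies both time points and no exception is stated, but it is not an explicit rule.
- **The power loss is conditional.** A reader might take about 51% as the power of the planned comparison. It is not: it holds only if the correlation is zero, and above 0.5 the change score would have more power than the post score. A low correlation is plausible when the baseline has no object to rate, but nothing in the documents establishes it.
- **The damage is contained.** A reader might infer a biased treatment comparison, and step 2 of the working shows why that does not follow. The post score remains interpretable in both arms, because both receive verbal and written advance care planning material. This is one secondary outcome of a self-described exploratory pilot.
- **Other remedies exist.** Adjusting the post score for baseline would avoid the variance penalty even at zero correlation. That is true, but it still means collecting a score whose referent is undefined unless the baseline items are reworded.

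**Conclusion.** The point holds in a limited form. On the article's own description, the PDMS is scheduled at a time when there is nothing for it to rate, and the general change analysis does not exempt it. Its baseline and change scores are therefore not interpretable as described. The schedule itself is stated, so this is more than a detail left to a fuller document.

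The between-arm comparison stays unbiased and the primary outcome, completion of advance care planning documents, is unaffected. The cost is interpretability of one of three secondary outcomes and possibly precision. Under equal standard deviations, power falls from 80% to between about 51% and 60% for correlations of 0 to 0.2, and does not fall at 0.5 or above. The interpretability problem does not depend on the correlation. It would ease only if the baseline items were shown to have a pre-intervention referent. The change is worth making but is not critical to the trial.

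**What to change.** - Remove the PDMS from the patient and caregiver baseline columns of Table 3.
- Add one sentence to the Statistical analysis section naming the between-arm difference in post-intervention PDMS score, with a 95% confidence interval, as the analysis. Randomisation makes this comparison valid without a baseline value.
- If baseline forms have already been collected, which is possible because the trial was registered retrospectively, do not analyse the PDMS as a change score. Base the comparison on post scores.
- If the baseline items were reworded so that they refer to something before the intervention, describe that version as an adaptation and use it at most as a covariate.

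The cost is one scale deleted from two baseline forms and one added sentence. If the forms are already in use, a change to the analysis text alone is enough. Removing the scale also shortens the baseline visit for participants.

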## Statistical analysis

Descriptive statistics will be presented as frequencies and relative frequencies for categorical variables, mean and standard deviation for normally distributed continuous variables, or median and interquartile range for continuous variables that are not normally distributed. We will examine secondary outcomes between the two groups comparing pre and pre and post-test intervention changes with Chi-square or Fisher’s exact test for categorical variables and two-sample *t*-tests or Mann-Whitney test for continuous variables.

Additionally, multiple linear regression will be performed, addressing the effect of socio-demographic and clinical variables to explore factors associated with the rates of completion of ACP All results obtained will be presented at a confidence interval of 95%. Thus *p* < 0.05 is assumed to be statistically significant. The statistical software SPSS 23 will be used in this analysis.

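### Continuous secondary scores are compared between arms without baseline adjustment; regressing the post score on arm and baseline would be more precise at almost no cost

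*Protocol article*

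**What the plan says.** The Statistical analysis section sets the method for the secondary outcomes: "We will examine secondary outcomes between the two groups comparing pre and pre and post-test intervention changes". For continuous scores the named tests are "two-sample *t*-tests or Mann-Whitney test for continuous variables". No baseline covariate is mentioned. The only regression in the section has a different purpose, "to explore factors associated with the rates of completion of ACP", so it does not adjust the secondary scores.

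Under Data collected and measures used, "Table 3 outlines the measures used at baseline and post-intervention". That table has ACP attitudes, the CCAT and the PDMS collected before and after the intervention from both patient and caregiver. Under Randomization and blinding, "Randomization occurs after completion of baseline assessments".

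The same measures section reports Cronbach alphas of .52 for CCAT-P, .50 for CCAT-F and .60 for CCAT-PF. It describes the PDMS as "a validated scale assessing patient and caregiver perception of an intervention’s usefulness".

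**The concern.** The trial asks every dyad for a baseline score and then uses it only by subtraction. Subtracting the whole baseline is the most efficient use of it only when the slope of post on pre is 1. When the slope is smaller, as is usual for questionnaire scores, subtraction adds baseline noise to the contrast. Regression estimates the slope from the data and removes only the part of the post score that baseline predicts.

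What is at stake is precision for the attitude and communication comparisons in a small trial. The Background notes that none of the reviewed video-tool trials looked at patient-caregiver communication, so the CCAT result is among the things this study would newly contribute, and the findings are meant to inform a later multisite trial. There is also a conditional issue: if the arms differ by chance at baseline, the change contrast moves in the opposite direction through regression to the mean.

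**Working it through.** **Inputs.** From Sample size and power: 43 dyads per group for analysis, 112 recruited, 30% dropout, 37% versus 67% completion, two-sided 5%, 80% power. From Randomization and blinding: 1:1 allocation, baseline before randomisation. Assumed, because the protocol gives no figure: the pre-post correlation r, shown from 0.3 to 0.9, and equal pre and post standard deviations (SD).

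**The plan's own figure.** With pooled variance and no continuity correction, n per arm = [1.96·√(2·0.52·0.48) + 0.8416·√(0.37·0.63 + 0.67·0.33)]² / 0.30² = (1.385 + 0.567)² / 0.09 = 42.3, so 43. The stated 43 reproduces (power 80.6%). It concerns the primary outcome and is used below only as the number per arm. No effect size or SD is stated for the secondary scores.

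**Variance per subject, in units of the score variance.**
- Change score: 2(1 − r)
- ANCOVA: 1 − r²
- Ratio, change to ANCOVA: 2(1 − r) / [(1 − r)(1 + r)] = 2/(1 + r)

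Detectable difference at 80% power = (1.960 + 0.842)·√(variance·2/43), in SD units.

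| r (assumed) | Change | ANCOVA | Ratio | Detectable, change | Detectable, ANCOVA |
|---|---|---|---|---|---|
| 0.3 | 1.40 | 0.91 | 1.54 | 0.715 | 0.576 |
| 0.5 | 1.00 | 0.75 | 1.33 | 0.604 | 0.523 |
| 0.7 | 0.60 | 0.51 | 1.18 | 0.468 | 0.431 |
| 0.8 | 0.40 | 0.36 | 1.11 | 0.382 | 0.363 |
| 0.9 | 0.20 | 0.19 | 1.05 | 0.270 | 0.263 |

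A ratio of 1.33 means that the change analysis needs 33% more dyads for the same precision. If 30% of the 112 recruited dyads are lost, 112 × 0.70 / 2 = 39 per arm remain, and every detectable difference rises by a factor √(43/39) = 1.05.

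**Unequal SDs.** With pre SD s₀ and post SD s₁, the change variance minus the ANCOVA variance is s₀² + s₁² − 2r·s₀s₁ − s₁²(1 − r²) = (s₀ − r·s₁)², which is never negative. The direction therefore does not depend on equal SDs, although the ratios in the table do.

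**Cost of the covariate.** At 86 dyads, estimating the slope inflates the ANCOVA variance by about 83/82 = 1.012. With equal SDs this outweighs the gain only when (1 + r)/2 × 83/82 exceeds 1, that is, for r above about 0.97.

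**Simulation** (4,000 trials per r, 43 per arm, illustrative effect 0.6 SD). Power for change versus ANCOVA was 0.794 versus 0.894 at r = 0.5 and 0.871 versus 0.928 at r = 0.6. Over r = 0.5, 0.6 and 0.8, type I error was 0.045 to 0.051 for both methods, and mean estimates were 0.600 to 0.605 for both.

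**Chance imbalance.** Given an observed baseline difference d between arms, the expected change contrast is the true effect minus (1 − r)d. At 43 per arm a one-standard-error imbalance is √(2/43) = 0.216 SD. With r = 0.5 the shift is 0.5 × 0.216, about 0.11 SD.

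**The other reading of the sentence.** The wording is garbled. If it means a comparison of post scores alone, the variance is 1 against 1 − r²: 0.91 at r = 0.3, 0.75 at 0.5, 0.51 at 0.7. ANCOVA is still the more precise.

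**The case against.** The strongest reply is that nothing here is an error. A two-sample test on change is valid in a randomised trial. The outcomes are secondary, the study calls itself exploratory and a pilot, no power is claimed for these scores, and a fuller analysis plan may exist. Most of this stands, and it limits the severity. It does not remove the point: the article names the tests itself, the better use of the baseline requires no further data, and a small study has most need of the precision.

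Three stronger readings are tempting, and the documents do not support them.

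- A reader might infer that the change-score analysis is biased. Over randomisation it is not, and the simulation shows none. The shift described above is conditional on the imbalance that happens to occur.
- A reader might take the CCAT alphas of .50 to .60 as showing that r is near or below 0.5, where change scores do no better than ignoring baseline. Alpha measures internal consistency, not the correlation between two occasions, and can understate reliability when items are heterogeneous. The figures suggest that r may be modest and no more. At r = 0.8 or 0.9 the loss is only 11% or 5%.
- A reader might conclude that Mann-Whitney has to be replaced by a bootstrap. That is a preference. The variance ratios apply to mean differences and do not carry over exactly to the rank test.

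**Conclusion.** The point holds as a loss of efficiency in a method that the protocol fixes. The unadjusted change-score comparison carries 5% to 54% more variance than ANCOVA for r between 0.9 and 0.3, and 33% more at r = 0.5. The size rests on an assumed r and equal SDs. The direction needs only that the slope of post on pre is not so close to 1 that one degree of freedom outweighs the gain. Conditional sensitivity to chance baseline imbalance is a second, smaller reason to adjust.

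The conclusion covers ACP attitudes and the CCAT scores. It does not extend to the PDMS: that scale rates how useful an intervention was, so a score taken before any intervention has doubtful meaning as a covariate. ACP completion, the primary outcome, is unaffected. Severity is modest, but the change is worth making because it is nearly free.

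**What to change.** Replace the test for these scores in the Statistical analysis section with a sentence to this effect: for ACP attitudes, CCAT-P, CCAT-F and CCAT-PF, the main between-arm comparison is a linear regression of the post-intervention score on arm and the baseline value of the same score, with patients and caregivers analysed separately and CCAT-PF analysed per dyad, reported as the adjusted mean difference with its 95% confidence interval. A bootstrap interval may be added for skewed residuals; this is optional. Repair the garbled wording of the current sentence at the same time.

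The cost is one sentence and one degree of freedom, about 1% of variance at 86 dyads. No additional data, visits or participants are needed, and SPSS, the software already named, fits the model.

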### Sample size and power

Based on the primary outcome of the completion of ACP documentation and assuming a completion rate of around 37% for the control group, with a total of 86 participants/dyads (43 per group) we will be able to show a significant improvement to 67% completion for the VDST group (power of 80%, two sided 5% significance level). Assuming an estimated dropout rate of 30%, recruitment of 112 dyads will be required. Based on previous published studies, we felt that a sample of this size would give us sufficient methodological experience to conduct a subsequent fully powered study [12].

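### The only inferential analysis named for ACP completion, the yes/no primary outcome, is an exploratory linear regression; the stated between-group tests are limited to secondary outcomes

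*Protocol article*

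**What the plan says.** All references are to the protocol article.

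- **Outcome assessment:** "The primary outcome measure will be the completion of ACP documentation". The individual parts of the plan are to be examined too. Each of these is also either completed or not, and no continuous completion score is defined.
- **Sample size and power:** the calculation compares two proportions, "assuming a completion rate of around 37% for the control group" against 67% in the video decision support tool (VDST) group, with "power of 80%, two sided 5% significance level". It gives 43 dyads per group, 86 in all.
- **Statistical analysis, first paragraph:** the two-group tests are introduced by "We will examine secondary outcomes between the two groups comparing pre and pre and post-test intervention changes". The sentence then lists chi-square or Fisher for categorical variables and t or Mann-Whitney for continuous ones.
- **Statistical analysis, second paragraph:** as an addition, "multiple linear regression will be performed, addressing the effect of socio-demographic and clinical variables to explore factors associated with the rates of completion". Study arm is not among the terms named, and no model for a binary outcome appears in the section.

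**The concern.** Read literally, the section gives a between-arm test to every outcome except the primary one. Where it does name an inferential method for completion, the method does not fit the kind of data.

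Two things are at stake:

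- **The arm comparison.** An analyst working from this text would have to infer which test answers the main question. The candidate tests do not all deliver the stated power.
- **The factor analysis.** A linear model on a 0/1 outcome can produce fitted probabilities below 0 or above 1. Its residual variance depends on the fitted mean. Its coefficients are differences in probability, not the odds ratios usually reported for such an analysis.

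**Working it through.** **1. Reproduce the plan's sample size.** Inputs from Sample size and power: p1 = 0.37, p2 = 0.67, difference 0.30, two-sided alpha 0.05, power 0.80. The pooled proportion is (0.37 + 0.67)/2 = 0.52.

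n per group = [1.960 × √(2 × 0.52 × 0.48) + 0.842 × √(0.37 × 0.63 + 0.67 × 0.33)]² / 0.30²
= [1.960 × 0.7065 + 0.842 × 0.6739]² / 0.09
= (1.385 + 0.567)² / 0.09 = 42.3, rounded up to **43**.

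This matches the plan. Other two-sided formulas give:

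| Formula | n per group |
|---|---|
| Pooled, no continuity correction | 43 |
| Arcsine | 43 (42.2 rounded up) |
| Unpooled | 40 |
| Pooled, continuity-corrected | 49 |

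The trial is therefore sized on a comparison of two independent proportions, which the Statistical analysis section does not assign to completion.

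**2. Power of the candidate tests at 43 per group.** The normal approximation gives 80.6%. Exact enumeration over all pairs of binomial counts gives:

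| Test | Power, 37% vs 67% | Type I error, both 37% |
|---|---|---|
| Pearson chi-square, uncorrected | 79.9% | 5.5% |
| Chi-square, continuity-corrected | 72.5% | 3.1% |
| Fisher's exact | 72.5% | 3.2% |
| Linear regression on arm alone | 79.0% | 5.3% |

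The uncorrected chi-square delivers the stated 80%; the two conservative tests lose about 7 points. The smallest expected cell count is about 43 × 0.48 = 20.6, so small cells give no reason to turn to Fisher.

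**3. Size of the problem with the linear model.** The baseline list in Data collected and measures used offers about 11 candidate predictors: eight items (age, sex, marital status, place of birth, relationship, primary diagnosis, time since diagnosis, prior prognosis discussion) and three DASS-21 subscales. The plan does not say that all would enter one model, so 11 is an assumption. The simulations used 78 dyads (112 × 0.70 = 78.4, the recruitment target less the stated 30% dropout), arm plus 11 independent normal covariates, four of them prognostic. The prognostic effects ran from 0 to 0.8 log-odds per standard deviation, also an assumption.

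- At least one fitted value fell outside 0 to 1 in about 80% to 100% of fits, affecting 4% to 13% of dyads.
- Covariates with no true effect were rejected 4.8% to 5.2% of the time at nominal 5%.
- Logistic regression with the same full set of terms rejected them 6.1% to 6.6% of the time.

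**4. Information available for a logistic model.** The expected number of non-completers is 78 × 0.48 ≈ 37, or 86 × 0.48 ≈ 41 if all 86 dyads are evaluable. With the last result in step 3, this argues for a short covariate list when the model is changed.

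**The case against.** The strongest reply is that the regression is explicitly supplementary and exploratory. A reader might infer that linear regression is the primary treatment test. The text does not support that: the regression is an add-on about socio-demographic and clinical correlates, which also explains why arm is not mentioned.

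A reader might also infer that the trial has no test for its main question. That goes too far. This is a condensed article, and a fuller analysis plan may name the test. The intended test can also be guessed: the secondary outcomes are scale scores, completion is the evidently categorical outcome, and a categorical test is listed. The limit to secondary outcomes may be loose drafting, as the same sentence contains another slip. Choosing between chi-square and Fisher is also ordinary analysis-plan detail.

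On harm, much of the defence stands. Non-constant variance is slight at the planned rates (0.37 × 0.63 = 0.233 against 0.67 × 0.33 = 0.221, ratio 1.05). With arm as the only term, linear regression performs almost as well as chi-square. Covariate p-values were not distorted in simulation, so a charge of overfitted p-values fails. Nothing in the section proposes predicting individual probabilities.

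What remains is what the text affirmatively says. It ties the two-group tests to secondary outcomes, and it names a model that does not suit a 0/1 outcome. A fuller plan could add a primary test, but these two sentences would still need correcting. Calling completion a rate does not change this, because it is observed once per dyad as yes or no.

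**Conclusion.** The point holds, and the text should be fixed. As written, the Statistical analysis section assigns no between-arm test to the primary outcome, and the only inferential model it names for that outcome is of an unsuitable type.

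The consequences are moderate. The planned 43 per group stands. The exploratory model would often give impossible fitted probabilities and would not report odds ratios, but its tests of covariates would be roughly valid. The 80% to 100% range is illustrative, since it depends on the assumed number of covariates and their effects.

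Naming the test matters because about 80% power at 37% versus 67% holds for the uncorrected chi-square, against about 72.5% for Fisher or the corrected version. It would be too strong to say that 43 per group reproduces only under the uncorrected chi-square formula, since the arcsine formula also gives 43.

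**What to change.** Change two sentences in Statistical analysis.

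1. Add a primary analysis statement, for example: *ACP completion will be compared between arms as the difference in proportions (VDST minus usual care) with a 95% confidence interval, tested by a two-sided Pearson chi-square test without continuity correction.*
2. Replace the linear model, for example: *Factors associated with completion will be explored by logistic regression including study arm and a small set of baseline covariates named in advance, reported as odds ratios with 95% confidence intervals.* How many covariates to allow is a judgement; the expected 37 to 41 non-completers argue for few.

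The cost is a text edit before analysis. The evaluable sample of 86 dyads, the questionnaires and data collection are unchanged. The uncorrected test has a slightly raised exact type I error (5.5% when both rates are 37%). If the team prefers Fisher or the corrected test, the stated power should be revised to about 72.5%, or the sample size recalculated (49 per group by the continuity-corrected formula).
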